### Statistical analysis {20a} {20b} {20c} {18b}

A descriptive analysis will be carried out for all the data collected. The normality of the data will be studied using the Kolmogorov–Smirnov and Shapiro–Wilk tests. For continuous quantitative variables, descriptions of central tendency and dispersion will be presented: mean and standard deviation respectively in case the variables follow a normal distribution or median and interquartile range for those variables that are not normally distributed. For categorical (qualitative) variables, frequencies and percentages will be presented. The main outcome (improvement > 2 points) will be tested using a generalized linear mixed model (GLMM). The GLMM model fit will include a between-subject factor and will also include a random effect for the time (baseline, 1st month, 3th month, 6th month, and 12th month) and the interaction between group and time variables. The inclusion of the interaction terms allows for a formal test between the groups over time. For the other variables, the mean effects of the interventions and the differences between groups and their respective 95% confidence intervals will be calculated using regression linear mixed models for repeated measures, which will incorporate terms for the treatment groups, time, and interaction terms. Treatment coefficients versus time interactions will be equivalent to the estimates of the differences between groups. All models will be adjusted for chance imbalances in outcome between groups at baseline. There will also be analyses of the covariates collected, including age, gender, and duration of symptoms. The analyses will follow the principles of intention to treat, and no interim analyses will be performed. No additional analysis will be performed. If a patient drops out of treatment, no additional outcome will be collected. The significance level will be set at 5%, and SPSS for Windows will be used for the statistical analysis.

The number of participants who complete the 12-month follow-up will be described by allocation; the study arms will be compared using chi-square tests and logistic regression to see if the attrition rate differs by arm and to compare baseline characteristics of participants who did and did not complete follow-up. Of those who complete follow-up, each variable will be examined for the presence of missing data, and if > 10% is observed for primary or secondary outcomes, then sensitivity analyses will be performed using complete case analysis or multiple imputation methods assuming data are missing at random (MAR). The MAR assumption indicates that the propensity for missingness does not depend on the unobserved outcome but rather is related to some other observed data.

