**Methods:**

We plan to conduct a randomized controlled study to compare the efficacy of PRF therapy plus ACS versus PRF therapy plus physiological saline 0.9% (PhS) on the DRG to reduce neuropathic pain in patients with persistent lower limb radiculalgia (LLR) and to contribute to the functional improvement and quality of life of these patients.

Study participants will include patients who meet study the inclusion/exclusion criteria. Eligible patients will be randomized in a 1:1 ratio to one of treatment with PRF plus ACS (experimental group) or PRF plus PhS (placebo group). The study group will consist of 70 patients (35 per group) who have experienced radicular pain symptoms for ≥ 6 months’ duration who have failed to respond to any therapy. Both groups will receive PRF on the DRG treatment before the injection of the sample (control or placebo). Patient assessments will occur at baseline, 1 month, 3 months, 6 months, and 12 months after therapy.

The primary efficacy outcome measure is Numeric Pain Rating Scale (NPRS) responders from baseline to 12 months of follow-up using validated minimal important change (MIC) thresholds. A reduction of ≥ 2 points in NPRS is considered a clinically significant pain relief.

The secondary efficacy outcome measure is the proportion of Oswestry Low Back Pain Disability Scale (ODS) responders from baseline to 12 months of follow-up in the experimental group (PRF plus ACS) versus the placebo group (PRF plus PhS). ODS responders are defined as those patients achieving the validated MIC of ≥ 10-point improvement in ODS from baseline to 12 months of follow-up as a clinically significant efficacy threshold.

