### Outcome measures and follow-up {12}

#### Primary outcome

The primary outcome will be level pain using Numeric Pain Rating Scale (NPRS). The NPRS is a segmented numeric version of the visual analog scale (VAS) in which a respondent selects a whole number (0–10 integers) that best reflects the intensity of his/her pain. A reduction of ≥ 2 points in NPRS is considered clinically significant pain relief [40]. This outcome will be measured at baseline at the moment of clinical interview and decision to recruitment and CI singed. This outcome will be measured again after the second intervention at 30 days, 3 months, 6 months, and 12 months after the intervention.

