### Sample size {14}

Based on the existing bibliography in relation to the treatment of pain by ACS treatment for other similar affections [32], it is estimated that accepting an alpha risk of 0.05 and a beta risk of 0.2 in a bilateral contrast, 35 subjects in the treatment group and 35 in the placebo group are needed to detect as statistically significant the difference between the proportion of patients with reduction pain of two points on the NPRS scale, which for the intervention group is expected to be 65%, and for the control group, it is expected to be 35%. A rate of loss to follow-up of 10% has been estimated.

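### The analysis section tests an NPRS improvement of more than 2 points, while the endpoint is defined as 2 points or more; on a whole-number scale these are different primary endpoints

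*Protocol article*

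**What the plan says.** Four places in the protocol article bear on the primary responder threshold.

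- **Abstract, Methods.** The primary efficacy measure is NPRS "responders from baseline to 12 months of follow-up using validated minimal important change (MIC) thresholds". The next sentence gives the threshold: "A reduction of ≥ 2 points in NPRS is considered a clinically significant pain relief".
- **Primary outcome.** The same cut-off is given, with a reference: "A reduction of ≥ 2 points in NPRS is considered clinically significant pain relief". This section also describes the NPRS as a scale "in which a respondent selects a whole number (0–10 integers").
- **Sample size.** The planning rates of 65% and 35% are for "the proportion of patients with reduction pain of two points on the NPRS scale". There is no inequality sign, but a patient with a two-point reduction plainly counts.
- **Statistical analysis.** "The main outcome (improvement > 2 points) will be tested using a generalized linear mixed model (GLMM"). This is the only place that says how the primary outcome is tested, and the only threshold in that section.

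**The concern.** On a continuous scale, the choice between a strict and a non-strict inequality would hardly matter. On the NPRS it moves a whole score category. The patients who change status are those whose improvement equals the protocol's own threshold for a meaningful reduction in pain.

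Three things are at stake. First, an analyst who codes from the analysis section tests a stricter endpoint than the one the trial defines and justifies by a minimal important change. Second, the 65% and 35% planning rates then no longer describe the tested endpoint. Third, with two published thresholds, either result could be presented as pre-specified. The article makes the main investigator responsible for data collection, outcome analyses and results. It gives only that person access to the final dataset, and it says no additional analysis will be done, so no planned sensitivity analysis would show the other threshold. This is a weakness in the text, not a suggestion about anyone's conduct.

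**Working it through.** **1. What the two thresholds mean.** Baseline and follow-up NPRS are integers from 0 to 10, so the change is an integer. Hence change > 2 is the same as change ≥ 3.

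| Improvement | Abstract and Primary outcome (≥ 2) | Statistical analysis (> 2) |
|---|---|---|
| 1 or less | non-responder | non-responder |
| exactly 2 | **responder** | **non-responder** |
| 3 or more | responder | responder |

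This step needs no assumption.

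**2. The plan's own figure.** Inputs from the Sample size section: 65% and 35%, two-sided alpha 0.05, power 80%, 35 per arm, 10% loss to follow-up. With pooled variance under the null,

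n = [1.960·√(2·p̄·q̄) + 0.842·√(p₁q₁ + p₂q₂)]² / (p₁ − p₂)²

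= [1.960·√0.5 + 0.842·√0.455]² / 0.30² = (1.386 + 0.568)² / 0.09 ≈ 42.4, so 43 per arm, and 43/0.9 = 47.8, so 48 per arm after 10% loss.

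The stated 35 does not reproduce under a two-sided test. Power at 35 per arm is

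Φ{(0.30·√35 − 1.386) / √0.455} = Φ(0.577) = 71.8%.

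The gap between 80% and 72% is a separate matter and is not due to the threshold. It is shown because 71.8% is the right baseline for the next step.

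**3. Illustrative effect of moving to ≥ 3.** The article gives neither an SD of change nor response rates at ≥ 3, so this step rests on assumptions: a normal underlying change with the same SD in both arms, rounded to integers, and calibrated so that P(change ≥ 2) is 65% and 35%. After rounding, ≥ 2 corresponds to an underlying value above 1.5, and ≥ 3 to one above 2.5. Then

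μ = 1.5 + SD·z(p), and P(≥ 3) = Φ(z(p) − 1/SD), with z(0.65) = 0.385 and z(0.35) = −0.385.

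For SD 2: Φ(0.385 − 0.5) = 45.4% and Φ(−0.385 − 0.5) = 18.8%.

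| Assumed SD | Rates at ≥ 3 | Fall per arm (points) | Difference between arms (points) | Power at 35 per arm | n per arm for 80% |
|---|---|---|---|---|---|
| Planned, ≥ 2 | 65% / 35% | – | 30.0 | 71.8% | 43 |
| 1.5 | 38.9% / 14.6% | 26.1 / 20.4 | 24.3 | 63.6% | 52 |
| 2.0 | 45.4% / 18.8% | 19.6 / 16.2 | 26.6 | 67.2% | 48 |
| 2.5 | 49.4% / 21.6% | 15.6 / 13.4 | 27.8 | 68.8% | 46 |
| 3.0 | 52.1% / 23.6% | 12.9 / 11.4 | 28.5 | 69.7% | 45 |

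The n column is before allowance for loss to follow-up.

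**4. Patients affected.** The fall per arm is the share improving by exactly 2 points. With 35 per arm, that is 35 × (0.196 + 0.162) = 12.5 patients at SD 2 and 35 × (0.129 + 0.114) = 8.5 at SD 3: roughly 8 to 13 of the 70.

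**The case against.** The strongest reply is that this is a slip. The strict sign appears once, in a parenthesis in a sentence whose purpose is to name the model. Where the threshold is presented as a criterion, it is ≥ 2, and no reason is given for a stricter cut-off. That reading is probably right, but it does not remove the problem: the parenthesis is the only threshold in the analysis section, and anyone coding from it would misclassify every patient with a two-point improvement.

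Some narrower points stand and limit what can be claimed.

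- The Primary outcome section does not use the word responder. It names the pain level as the outcome and supplies the cut-off; the responder definition comes from reading it with the abstract.
- The Sample size section has no inequality sign. A two-point reduction fits ≥ 2 best, but that is an inference.
- The rates at ≥ 3 depend on an assumed distribution. The fall is largely common to both arms, so the difference narrows only from 30 to about 27–28 points and power by 2 to 5 points for an SD of 2 to 3.
- An analysis plan that is not shown may settle the matter, so it is not established that the choice would still be open at unblinding. Even so, the published protocol contradicts itself, which is different from leaving a detail out.

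**Conclusion.** The concern holds. The threshold in the analysis section is wrong as written: it disagrees with the abstract and the Primary outcome section, and with the natural reading of the Sample size section. That conclusion needs only the integer scale and the quoted text.

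The size is less certain. For an assumed SD of change of 2 to 3 points, response rates fall by about 11 to 20 points per arm, and power at 35 per arm falls from about 72% to 67–70%. At an SD of 1.5 it would be about 64%. The power loss is secondary. What makes this a must-fix is that it concerns the definition of the primary endpoint, can change the primary result, and leaves two thresholds in print.

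**What to change.** In the Statistical analysis section, change the parenthesis that defines the main outcome from an improvement of > 2 points to an improvement of ≥ 2 points, with improvement meaning baseline NPRS minus follow-up NPRS. Add the ≥ sign to the Sample size section so that all four places agree.

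If the corrected sentence also names 12 months, note that only the abstract ties the responder to that visit. The Primary outcome section lists all follow-up visits and the model uses them all, so fixing the time point is a further decision and should be made openly.

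The cost is one symbol in the analysis section and one clarification in the sample size text. The planning rates do not change, and the correction alone does not alter the required sample size. It should be recorded as a dated amendment, and carried into any analysis plan, before database lock and unblinding.

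### The only between-group test named is the group-by-time interaction, which does not target the declared month-12 NPRS responder endpoint; the declared ODS responder endpoint has no inferential analysis

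*Protocol article*

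**What the plan says.** The Methods part of the abstract defines both efficacy endpoints as responder outcomes over 12 months. The primary one is "The primary efficacy outcome measure is Numeric Pain Rating Scale (NPRS) responders from baseline to 12 months of follow-up", with a threshold of at least 2 points. For the secondary, "The secondary efficacy outcome measure is the proportion of Oswestry Low Back Pain Disability Scale (ODS) responders from baseline to 12 months of follow-up" is compared between arms, a responder being a patient "achieving the validated MIC of ≥ 10-point improvement in ODS from baseline to 12 months of follow-up".

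The Sample size section matches the primary endpoint. It sizes a two-sided comparison of two NPRS responder proportions, 65% vs 35%, with 35 patients per arm.

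The Primary outcome section is looser: "The primary outcome will be level pain using Numeric Pain Rating Scale (NPRS"). It then gives the 2-point criterion and lists four follow-up visits, without singling out month 12.

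The Statistical analysis section fits a GLMM to NPRS improvement, with group, time (baseline and months 1, 3, 6 and 12) and their interaction. Its one statement of a between-group test is "The inclusion of the interaction terms allows for a formal test between the groups over time". ODS falls under the next provision: "For the other variables, the mean effects of the interventions and the differences between groups" come from linear mixed models. The section also says that no further analyses are planned.

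**The concern.** A trial sized on a difference in responder proportions, with a 12-month endpoint, should be decided by that difference at month 12. An interaction test asks something else, and what it asks depends on whether baseline is a time level.

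- **Without baseline**, it asks whether the treatment effect changes between visits. A stable benefit is then a null result.
- **With baseline**, it asks whether there is a difference at any visit. An early benefit that has gone by month 12 can make it significant.

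Either way, the test result and the 12-month claim can part company. For ODS, the declared proportion has no test or interval at all, so the secondary claim would rest on a mean difference that the abstract does not name as the endpoint.

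**Working it through.** **Inputs from the article.** 35 per arm; 65% vs 35%; two-sided 5%; power 80%; loss 10% (Sample size). Visits at baseline and months 1, 3, 6 and 12 (Statistical analysis).

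**The plan's own figure.** For a two-sided comparison of 65% vs 35% with pooled variance:

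n = [1.960·√(2·0.5·0.5) + 0.842·√(0.65·0.35 + 0.35·0.65)]² / 0.30² = (1.386 + 0.568)² / 0.09 ≈ 42.4, so 43 per arm, or 43/0.9 ≈ 48 after 10% loss.

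The stated 35 is not reproduced. At 35 per arm, power is Φ[(0.30·√35 − 1.386)/0.675] = Φ(0.577) ≈ 0.72. The shortfall is a separate matter. It is shown here because about 0.7 is the benchmark for a direct month-12 test.

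**What each test asks.** Let d(t) be the difference in responder proportion at visit t.

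- Declared endpoint: d(12) = 0.
- Interaction, post-baseline visits only (3 df): d(1) = d(3) = d(6) = d(12).
- Interaction with baseline as a time level (4 df): d(0) = d(1) = d(3) = d(6) = d(12). Nobody can have improved on baseline at baseline, so d(0) = 0 by construction, and the hypothesis becomes that all four later differences are zero.

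Neither interaction hypothesis is d(12) = 0.

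**Simulation.** 4,000 trials per scenario, 35 per arm, complete data. Correlated binary responses come from a latent normal with correlation 0.3, 0.6 or 0.8. The interaction is a Wald test on the risk-difference scale, standing in for the GLMM test; month 12 uses the two-proportion z-test. Trajectories and correlations are assumptions, and ranges run over the correlations.

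- *Constant 65% vs 35% at all four visits:* 3-df interaction 6 to 7%; 4-df interaction 73 to 93%; month-12 test 69 to 72%.
- *Placebo fading 55/50/40/35%, ACS at 65%:* 3-df interaction 24 to 40%; month-12 test about 70%.
- *Early benefit only, ACS 65/60/45/35%, placebo 35%:* 3-df interaction about 50 to 72%; 4-df interaction 76 to 81% (74 to 81% on a repeat with another seed); month-12 test about 5%.

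With no interaction present the 3-df test rejects in about 6.6%, and under no effect the 4-df test in 7 to 8%, so both are mildly anti-conservative. The 6 to 7% in the first scenario is therefore simply the test's false-positive rate.

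**The model as written, on the logit scale.** With baseline as a time level, responders are 0 of 35 in both arms there, and the baseline log-odds has no finite estimate. A logistic fit to one simulated data set gave standard errors of about 2.2×10⁴ for the time terms and 3.1×10⁴ for the group-by-time terms. The month-12 interaction coefficient was 1.30 with a standard error of 3.1×10⁴, which is unusable.

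**ODS.** Set side by side, the abstract declares a proportion of patients improving by 10 points or more, and the analysis section provides a linear model for the mean. No provision for a between-group comparison of the proportion appears anywhere in the article.

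**The case against.** The best defence is that the NPRS responder variable is modelled, with month 12 as one of its time levels, and that the interaction is said only to allow a formal test, not to be the sole decision rule. That stands. A reader might infer that the plan leaves NPRS responders unanalysed; the article does not support this, since a month-12 contrast can be drawn from a post-baseline version of the model. The fault is that the named test is a different one and the contrast is not named.

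A reader might also infer that, under this plan, a constant benefit must give a null interaction. That holds only if baseline is left out. The article lists baseline as a time level, and on a risk-difference scale the test then detects a constant benefit in 73 to 93% of trials.

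The section also equates interaction coefficients with group differences. That is standard for continuous scores with a genuine baseline measurement, and the sentence follows the linear-model text. It does not carry over to a responder variable that is zero for everyone at baseline.

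A third tempting inference is that any of four visits could be presented as primary. The abstract fixes 12 months, which limits this. The best-of-four error of 1 − 0.95⁴ = 18.5% assumes independent visits; under the assumed correlations it is roughly 13 to 19%, the top of that range reflecting the z-test's own small-sample error.

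The Primary outcome wording is loose rather than a firm contradiction, since the 2-point criterion follows. A statistical analysis plan could name the contrast, but the article itself states which test and models are used. On ODS, the defence can say only that the endpoint is secondary, that categorical variables are described by frequencies and percentages, and that the mean gets a 95% confidence interval. None of these is an inferential comparison of the declared proportion.

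**Conclusion.** The point holds in this form: the named formal test does not target the month-12 NPRS responder endpoint that the abstract declares and the sample size assumes, and the declared ODS responder proportion has no inferential analysis.

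The NPRS fault survives either reading of the model. Without baseline, the interaction has almost no chance of detecting a constant benefit (6 to 7%, against about 70% for the month-12 test). With baseline, a logistic model separates; on a risk-difference scale the interaction is an omnibus test that is significant in about 76 to 81% of trials with an early benefit and no month-12 difference.

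The percentages depend on assumed trajectories, correlations of 0.3 to 0.8, complete data at 35 per arm and a Wald stand-in for the GLMM. The mismatch of hypotheses, the structural zero at baseline and the ODS gap depend on none of these.

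**What to change.** 1. Fit the NPRS responder GLMM to the post-baseline visits only (months 1, 3, 6 and 12).
2. Name one primary test: the month-12 between-group contrast in NPRS responders from that model, with a 95% confidence interval, two-sided at 5%. Make the other visits and the interaction supportive.
3. Analyse ODS responders (10 points or more) at month 12 in the same way, and keep the linear model for mean ODS as supportive.
4. Align the Primary outcome section with the abstract, so that the responder definition and month 12 appear in both. The Statistical analysis section writes the NPRS cut as more than 2 points and the abstract as at least 2; on a whole-number scale these differ, so one threshold should be used throughout.

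The cost is protocol and analysis wording, with no new data and no change to visits. The change should be made and dated before the allocation is unblinded.

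### The trigger for a missing-data sensitivity analysis counts only patients who complete follow-up, so dropout cannot set it off, and neither method it allows probes the missing-at-random assumption

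*Protocol article*

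**What the plan says.** All references are to the protocol article.

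- **Statistical analysis, attrition.** Completion of the 12-month follow-up is described by arm. Attrition is compared between arms by chi-square tests and logistic regression, and baseline characteristics are compared between those who did and did not complete.
- **Statistical analysis, trigger.** "Of those who complete follow-up, each variable will be examined for the presence of missing data". If more than 10% is missing for a primary or secondary outcome, "sensitivity analyses will be performed using complete case analysis or multiple imputation methods assuming data are missing at random (MAR".
- **Sample size.** "A rate of loss to follow-up of 10% has been estimated".
- **How outcome data stop.** Data collection and Statistical analysis end outcome collection when a patient leaves the study or drops out of treatment. Monitoring, safety, and quality control allows withdrawal after an adverse effect. Pain management excludes data from the date of a new infiltration or surgery in the same area.
- **Main analysis.** Intention to treat, with a generalised linear mixed model for the primary responder outcome and linear mixed models for the other outcomes.

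**The concern.** A sensitivity rule should respond to the missingness that most threatens the result. In a 12-month pain trial that is mainly patients who leave. Here a patient who seeks a new infiltration or surgery, or is withdrawn after an adverse effect, is plausibly not responding well, so the chance of being missing may depend on pain that is never recorded. The rule excludes exactly these patients from the count that decides whether a sensitivity analysis is run.

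The methods have the same limit. A mixed model handles dropouts properly only if data are MAR given what was observed. Imputation under MAR repeats that assumption, and complete case generally needs a stronger one and sits badly with intention to treat. At stake is whether a positive 12-month responder result can be shown not to depend on what happened to the patients who left.

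**Working it through.** **Inputs.** 35 per arm, 70 in total; responder rates 65% vs 35%; 10% loss (all from Sample size); trigger of more than 10% missing among completers (Statistical analysis). The split of losses between arms is my assumption, because the article gives none.

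**1. The plan's own figure.** 10% of 70 = 7 lost, leaving 63 completers. (The 35 per arm does not itself reproduce: the pooled two-sided formula gives 43 per arm before loss. That is a separate matter, and nothing below depends on it.)

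**2. What the rule sees.** Missingness under the rule = completers lacking the outcome ÷ completers.
- 7 lost, 63 full records: 0/63 = 0%. No trigger.
- 20% lost (14): 0/56 = 0%. 30% lost (21): 0/49 = 0%. No trigger.
- 7 lost and 6 of the 63 completers also lacking the outcome: 6/63 = 9.5%. No trigger, although (7 + 6)/70 = 18.6% of randomised patients have no outcome.

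**3. Would changing the denominator be enough?** 7/70 = 10.0%, which does not exceed 10%. At exactly the expected loss the rule would still be silent, so the threshold has to go as well.

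**4. Illustration of what could go unseen.** Pooled two-proportion z-test at 12 months, a simple stand-in for the mixed model: z = (p1 − p2) / √[p(1 − p)(1/n1 + 1/n2)], with p the pooled proportion. Responder counts among completers are the planned rates, rounded.

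Worked case, all 7 losses in the serum arm:
- Completers 18/28 vs 12/35: p = 30/63 = 0.476, SE = 0.127, z = 0.300/0.127 = 2.37, p-value 0.018.
- Lost as non-responders, 18/35 vs 12/35: p = 30/70 = 0.429, SE = 0.118, z = 0.171/0.118 = 1.45, p-value 0.15.

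| Losses (serum, saline) | Completers | Lost as non-responders | Serum lost fail, saline lost respond |
|---|---|---|---|
| 7, 0 | 18/28 vs 12/35, p=0.018 | 18/35 vs 12/35, p=0.15 | same as previous column |
| 3, 4 | 21/32 vs 11/31, p=0.017 | 21/35 vs 11/35, p=0.016 | 21/35 vs 15/35, p=0.15 |
| 4, 3 | 20/31 vs 11/32, p=0.017 | 20/35 vs 11/35, p=0.030 | 20/35 vs 14/35, p=0.15 |
| 4, 4 (8 lost, 11.4%) | 20/31 vs 11/31, p=0.022 | 20/35 vs 11/35, p=0.030 | 20/35 vs 15/35, p=0.23 |
| 0, 7 | 23/35 vs 10/28, p=0.018 | 23/35 vs 10/35, p=0.002 | 23/35 vs 17/35, p=0.15 |

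In every row the completers have complete records, so no sensitivity analysis would be triggered.

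**5. Does the attrition comparison fill the gap?** For a 7–0 split it would raise a flag: 7/35 vs 0/35 gives z = 0.200/√(0.1 × 0.9 × 2/35) = 2.79, p = 0.005. The plan attaches no outcome analysis to that flag. A baseline comparison also cannot show whether leaving depended on later, unrecorded pain.

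**The case against.** The other side has several good points.

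- **Attrition is examined.** A reader might infer that the plan ignores dropouts when it looks at missing data. It does not: attrition is compared by arm, and non-completers are compared with completers at baseline. Only the trigger for an outcome sensitivity analysis leaves them out.
- **The main model uses dropouts' earlier visits.** That is right, and the re-intervention rule excludes data only from the date of the new procedure. But using those visits to stand for later ones rests on MAR.
- **The rule is not empty.** It would be too strong to say that it can never fire. A completer can miss month 1, 3 or 6, or leave a questionnaire incomplete. It fails for dropout, not for intermittent gaps.
- **An analysis departing from MAR may be in the statistical analysis plan.** Its absence from an article would not by itself be a finding. Here, however, the article states a rule with a denominator, a threshold and methods, and it is the stated rule that fails. The sentence ruling out additional analyses should not be read as barring sensitivity analyses, since the same section goes on to plan some.
- **Complete case and imputation are not mere repeats of the mixed model.** Complete case rests on a different assumption, and imputation can bring in auxiliary variables. That stands, but neither lets missingness depend on the unseen outcome.
- **The large p-values are selected.** For near-balanced loss, the worst cases need serum dropouts to fail and saline dropouts to respond. They are bounds, not forecasts. Plain non-responder imputation leaves the near-balanced examples significant, and loss confined to the saline arm strengthens them.

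**Conclusion.** The concern holds as a defect in the trigger and in the methods it permits. Dropout cannot trigger an outcome sensitivity analysis at any rate, including the 10% that the plan expects, and up to 13 of 70 outcomes (18.6%) could be missing at that rate without one. If the rule fires on gaps among completers, neither option tests the MAR assumption.

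The effect on the result depends on how losses divide between arms. Concentrated in the serum arm and counted as non-response, the expected 7 losses move p from 0.018 to 0.15. Near-balanced loss counted the same way leaves p at about 0.02 to 0.03. The opposite-direction cases (p = 0.15 to 0.23) are limits only. These figures rest on the planned 65% and 35% holding among completers, on assumed splits of the losses, and on a two-proportion test in place of the mixed model.

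A reader might infer that the trial's result will be unreliable, or that informative dropout is established. The documents support neither. They show that the article's rule would not reveal whether the conclusion depends on the dropouts. This should be corrected before the data are analysed.

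**What to change.** In the Statistical analysis section and the statistical analysis plan:

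1. Assess missing NPRS and ODS in all randomised patients, by arm and at each visit, with reasons for leaving. Keep the existing attrition and baseline comparisons.
2. Remove the 10% threshold and run the sensitivity analyses whatever the amount missing.
3. For the primary outcome, pre-specify (a) non-responder imputation and (b) delta-adjusted multiple imputation by arm, with deltas increased until the conclusion changes (tipping point). The two are complementary, since (a) alone changes little when loss is balanced.
4. Keep complete case at most as a supplementary analysis, not as an alternative to imputation.

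The cost is revised wording and a few hours of extra analysis. No new patients, visits or data are needed. The change does not recover outcomes that are no longer collected after a patient leaves; it shows how far the conclusion depends on them.
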